### Data collection and management

The chief investigator will be responsible for the data collection and management. Deidentified data will be stored in a password protected Research Electronic Data Capture (REDCap) system hosted at King Edward Memorial Hospital [31]. REDCap is a secure, web-based application designed to support data capture for research studies, providing: (1) an intuitive interface for validated data entry; (2) audit trails for tracking data manipulation and export procedures; (3) automated export procedures for seamless data downloads to common statistical packages; and (4) procedures for importing data from external sources [31]. Only authorised persons will have access to the data. The consent forms and associated paperwork available in the hard copy will be stored securely to maintain privacy and confidentiality of research participants. AR, SP, KS and JP will have access to the final data set.

### Sample size

The normal SpO_2_:PiO_2_ curve in adults is shifted to the right of oxygen-haemoglobin dissociation curve by 6 kPa. Preterm infants with moderate to severe BPD have a mean (SD) shift of 16.5 (4.7) kPa [19]. We estimate that up to 20% of the recruited infants may not have SpO_2_-PiO_2_ measurement done at 36 weeks due to death, withdrawal of consent, and transfer of the patient to other hospitals. Allowing for this 20% loss of the cohort before measurement of the primary outcome, the required sample size is 188 (94 in each group) to detect a 20% change in the rightward shift in the treatment group compared with the control (power 80% with two-tailed test, significance 5%). An average of 110 infants less than 28 weeks gestational age are born per year at King Edward Memorial Hospital. All infants admitted in the neonatal intensive care unit will be screened daily to identify eligible infants. We expect to complete the recruitment in less than 3 years.

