## Background

Bronchopulmonary dysplasia (BPD) is a major respiratory morbidity associated with premature birth and affects 41% of the infants born before 28 weeks of gestational age [1]. BPD is associated with significant long-term health-consequences, which may persist to school age and adolescence. Infants with BPD are more likely to have chronic cough and asthma like symptoms in school age, abnormal lung function and lung imaging in adolescence, and greater need for hospitalisation and respiratory morbidity as compared with premature infants of similar gestational age without BPD [2–4]. Even more importantly, BPD may adversely influence long-term neurodevelopmental outcomes [5–7]. The current armamentarium for prevention of BPD includes surfactant, caffeine, lung protective ventilation strategies, and targeted oxygen saturation. BPD remains a heavy burden on healthcare resources despite current integrated approaches to therapy for BPD.

Low plasma and tissue concentrations of vitamin A in very low birthweight (VLBW) infants may contribute to the pathophysiology of BPD [8]. Intramuscular (IM) vitamin A supplementation decreases the incidence of BPD in VLBW infants [9, 10]. However, the practice of IM vitamin A supplementation is not widely accepted because of the discomfort and risk of trauma associated with repeated IM injections [11]. In addition, high cost and limited availability of Vitamin A parenteral preparations may further deter physicians from the use of IM vitamin A for prevention of BPD [12]. The intravenous (IV) route of administration is invasive, difficult to maintain for a long term, and associated with increased risk of infection: hence IV administration of Vitamin A is not suitable for prolonged duration of preventive therapy in preterm infants.

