Our objective is to undertake a randomised controlled trial to determine if extremely preterm infants (< 28 w gestation) receiving enteral water soluble Vitamin A supplements from commencement of enteral feeds until 34 w PMA compared to a placebo enteral supplement, will have a reduced severity of BPD at 36 w PMA (Additional file 1). We hypothesize that compared to placebo, enteral supplementation with water-soluble vitamin A will decrease the severity of BPD as measured by right shift in the peripheral oxyhaemoglobin saturation versus partial pressure of inspired oxygen (SpO_2_-PiO_2_) curve [19]. We will define a clinically significant reduction in BPD severity as a 20% decrease in the right shift of the SpO_2_-P_i_O_2_ curve: this change approximates the shift required to change from severe BPD to moderate BPD, moderate BPD to mild BPD, or mild BPD to no BPD (unpublished observations, [name]).

A sub-study will evaluate the utility of salivary retinol for assessment of Vitamin A status (Vitamin A plasma-saliva correlation sub-study). Use of saliva for the measurement of hormones and vitamins is gaining attention because of its ease of collection, painless nature and low potential for patient harm. Adult salivary and plasma retinol are correlated strongly [20]. A strong correlation of salivary and plasma retinol in very preterm infants will facilitate development of acceptable and non-invasive assessment of vitamin A status in these infants.

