**Fig. 1 Fig1:**
[figure not shown]
EVARO study schedule. PMA: Post menstrual age

Inclusion criteria:Infants born at less than 28 weeks’ gestational age.Less than 72 h after birth.Informed and signed consent from the parents or legal guardian

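### The sample size rests on the shift seen in moderate to severe BPD, so the stated 80% power is not shown to hold for the whole under-28-week cohort

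*Protocol article*

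**What the plan says.** All of this is in the protocol article.

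- **Planning inputs (Sample size).** There is one mean and SD: "Preterm infants with moderate to severe BPD have a mean (SD) shift of 16.5 (4.7) kPa [19". The same section gives a normal reference: the "curve in adults is shifted to the right of oxygen-haemoglobin dissociation curve by 6 kPa".
- **Target and size (Sample size).** After a 20% allowance for missing measurements, the article gives its total: "the required sample size is 188 (94 in each group". The purpose that it attaches to this number is "to detect a 20% change in the rightward shift in the treatment group compared with the control (power 80% with two-tailed test, significance 5". The base of the 20% and its value in kPa are not given.
- **Who is enrolled (inclusion and exclusion criteria).** "Infants born at less than 28 weeks’ gestational age", less than 72 h old and with consent. Only major congenital gut or airway abnormalities exclude. No criterion concerns BPD or respiratory risk.
- **Who is analysed (Statistical analysis).** The mean shift is compared between arms by intention to treat with Student's t test. The comparison is not limited to infants with BPD.
- **How common BPD is (Background).** BPD "affects 41% of the infants born before 28 weeks of gestational age [1"]. No grade is attached.
- **How the shift relates to BPD.** The Primary outcome section says that the shift correlates with severity. The Background says of a 20% decrease that "this change approximates the shift required to change from severe BPD to moderate BPD", and likewise for each lower step.

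**The concern.** The planning figures and the analysis describe different groups of infants. If 41% develop BPD, and the shift rises with severity, the average over everyone measured at 36 weeks should lie below the average in moderate to severe disease. A percentage target then means fewer kPa. The spread also changes, because the cohort mixes infants with and without substantial disease. The article gives no whole-cohort mean or SD and no reason for carrying the subgroup figures over.

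At stake is how a null result would be read. The Discussion presents a favourable result as opening the way to a multicentre trial. If no difference is found, readers will set that against a claimed 80% power to detect a 20% change, and that claim has been worked out only for the diseased subgroup.

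**Working it through.** **Inputs from the article.** Subgroup mean 16.5 kPa and SD 4.7; normal shift 6 kPa; 20% change; 80% power; two-sided 5%; 94 per arm; 20% loss; BPD 41%. Evaluable per arm: 94 × 0.8 = 75.2, taken as 75.

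**1. Reproduce 188.** Per arm, n = 2 × (1.960 + 0.842)² × SD² / δ².

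- 20% of the whole shift: δ = 0.2 × 16.5 = 3.3 kPa, so n = 31.8. That is 40 per arm after dividing by 0.8, or 80 in all. It does not give 188.
- 20% of the excess over normal: δ = 0.2 × (16.5 − 6) = 2.1 kPa, so n = 78.6. Times 1.2 this is 94.4 per arm, which matches the stated 94.

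So the stated size comes from the moderate-to-severe figures, on the excess scale. Power at 75 per arm with these inputs is 78% (noncentral t). Dividing by 0.8 instead of multiplying by 1.2 would give 99 per arm, but that is a separate matter.

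**2. Lower the mean only, keeping SD 4.7 and 75 per arm.**

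- Mean 14 kPa: δ = 0.2 × 8 = 1.6 kPa, power 54%.
- Mean 12 kPa: δ = 1.2 kPa, power 34%.

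To keep the planned ratio of difference to SD at a mean of 14 kPa, the SD would have to fall to 4.7 × 1.6 / 2.1 = 3.6 kPa.

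**3. Illustrate with a mixture.** Let 41% have 16.5 (4.7) kPa and 59% have mean b and SD s. The values of b and s are **assumptions**; the article gives none.

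Mean = 0.41 × 16.5 + 0.59 × b

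Variance = 0.41 × 4.7² + 0.59 × s² + 0.41 × 0.59 × (16.5 − b)²

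Example with b = 12, s = 2: mean = 6.765 + 7.08 = 13.8; variance = 9.06 + 2.36 + 4.90 = 16.3; SD = 4.04.

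| b | s | cohort mean | cohort SD | 20% of excess (kPa) | power for that | power for fixed 2.1 kPa |
|---|---|---|---|---|---|---|
| 6 | 2 | 10.3 | 6.17 | 0.86 | 14% | 54% |
| 6 | 4.7 | 10.3 | 6.98 | 0.86 | 12% | 45% |
| 8 | 2 | 11.5 | 5.38 | 1.10 | 24% | 66% |
| 8 | 4.7 | 11.5 | 6.29 | 1.10 | 19% | 53% |
| 10 | 2 | 12.7 | 4.65 | 1.33 | 41% | 78% |
| 10 | 4.7 | 12.7 | 5.68 | 1.33 | 30% | 61% |
| 12 | 2 | 13.8 | 4.04 | 1.57 | 66% | 89% |
| 12 | 4.7 | 13.8 | 5.20 | 1.57 | 45% | 69% |

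On the scale that yields 188, power is 12–66%. For a fixed 2.1 kPa it is 45–89%. The cohort SD runs from about 4.0 to 7.0, so it can lie on either side of 4.7.

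**4. Vary the 41%.** With 30% or 60% in its place, b of 6–12 and s of 1.5–4.7, power on the excess scale is 8–72% (normal approximation).

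**5. Detectable difference at 75 per arm.** 2.802 × √(2/75) × SD = 0.457 × SD, which is about 2.15 kPa at SD 4.7 and 2.9 kPa at SD 6.4.

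**The case against.** The strongest reply is that the size of any loss rests on values the article does not supply. The 6 kPa floor is an adult norm, not shown to apply to extremely preterm infants at 36 weeks. At a mean of 12 kPa and SD 2–3 for the remaining infants, the cohort SD is 4.0–4.4 and power for a fixed 2.1 kPa is 83–89%. If the 20% is meant of the whole shift, power under the assumptions in the table is 44–99%. All of this stands, and it rules out three stronger readings that a reader might infer:

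- *The cohort SD must exceed 4.7.* It need not; the mixture goes both ways.
- *Most analysed infants will be free of BPD and near normal.* The 41% is ungraded. If it counts only moderate to severe disease, the other 59% include mild cases. If it counts any BPD, fewer than 41% may match 16.5 (4.7).
- *Infants with BPD would have to improve by far more than planned to carry those with no severity step to gain.* That argument takes 20% of the whole shift, which does not produce 188. On the excess scale an infant already at 6 kPa is assigned no improvement.

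It is also fair to say that the planning SD affects neither bias nor type I error, and that the result will be reported with a 95% confidence interval, by which a null finding can be judged. That limits the harm. It does not make the stated power right for the analysed cohort.

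**Conclusion.** The mismatch is documented: subgroup inputs, whole-cohort enrolment and analysis, and nothing in the article to connect them. The stated 80% power is therefore not shown to apply to the infants who will be analysed.

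The direction is firm only on the scale that reproduces 188. There, power fell below 80% in every mixture tried, and a cohort mean below 16.5 kPa lowers it unless the SD falls in proportion to the excess over 6 kPa. That scale is itself inferred from the arithmetic, because the article does not say what the 20% is of.

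The size is not established. The 12–66% and 45–89% ranges rest on assumed values for infants outside the moderate-to-severe group. A reader might conclude that the trial is underpowered as a matter of fact. The documents do not support that; they show only that adequate power has not been demonstrated.

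**What to change.** In the Sample size section:

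1. Replace 16.5 (4.7) kPa with the expected mean and SD for all infants under 28 weeks measured at 36 weeks' PMA. Use severity-specific shifts weighted by their expected frequency, or the unit's own 36-week data, and name the source.
2. State the 20% target in kPa, and whether it is 20% of the whole shift or of the excess over 6 kPa.
3. Restate the power for that target at about 75 evaluable infants per arm, or give the detectable difference as 0.457 × SD for a plausible range of SDs.

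The cost is a rewritten paragraph and a look at existing data. The number recruited, eligibility and treatment need not change. The drawback is that the stated power will probably be less favourable than 80% if the excess scale is kept.

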### Statistical analysis

The data will be analysed statistically based on “intention to treat” using a statistical package (SPSS, version 24.0, IBM Corporation and others, USA). The primary outcome of right shift in the SpO_2_-PiO_2_ curve is a continuous outcome and will be reported as mean ± standard deviation for the intervention and control study groups. The primary outcome will be compared between the two groups using Student’s t test and the result will be reported as “mean difference with 95 % confidence intervals”.

Secondary outcomes will be compared between the two groups using χ^2^ test for categorical data and either the Mann-Whitney U test (not normally distributed) or Student’s t test (normally distributed) for continuous data. The correlation between serum and salivary vitamin A levels, and blood and saliva RDR values will be tested using Pearson r correlation analysis. Bland-Altman analysis will be used to analyse agreement between two assays. A “p” value of <0.05 will be considered statistically significant.

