### Randomisation and allocation concealment

The infants will be stratified for randomisation according to the sex and gestational age at birth (23^0^ to 25^6^ and 26 to 27^6^ weeks). Infants will be randomised to treatments by the hospital pharmacist using a computer generated random table (REDCap) in blocks of six within the REDCap randomisation module [31]. The pharmacist will not have any clinical information regarding the recruited infant apart from stratification group and infant sex.

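### Randomisation is stratified by sex and gestational age, but the primary t test ignores both; if the strata predict right shift, the test is conservative and precision is forgone

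*Protocol article*

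**What the plan says.** Under Randomisation and allocation concealment, the protocol article states: "The infants will be stratified for randomisation according to the sex and gestational age at birth". There are two gestational bands, split at 26 weeks, so there are four strata, and allocation is "in blocks of six within the REDCap randomisation module".

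Under Statistical analysis, the primary comparison is fixed: "The primary outcome will be compared between the two groups using Student’s t test and the result will be reported as" a mean difference with 95% confidence interval. The article mentions no adjustment for sex or gestational age.

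Under Sample size, "the required sample size is 188 (94 in each group"), chosen "to detect a 20% change in the rightward shift in the treatment group compared with the control (power 80% with two-tailed test, significance 5"%). The inputs given are these: "Preterm infants with moderate to severe BPD have a mean (SD) shift of 16.5 (4.7) kPa"; a normal adult curve "shifted to the right of oxygen-haemoglobin dissociation curve by 6 kPa"; and a 20% loss before the primary measurement.

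Under Intervention, in justifying dose and duration, the article says that smaller infants are at higher risk of BPD and that vitamin A stores fall with decreasing gestation. It makes no such statement about sex.

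**The concern.** Stratified blocks keep the arms close to balanced on sex and gestational band. Differences between strata therefore contribute little to the true sampling error of the treatment difference. The two-sample t test does not know this: it estimates its standard error from the overall SD, which still contains the between-stratum variation. If the strata are prognostic, the standard error is too large, the 95% interval covers more than 95% of the time, and the test rejects less than 5% of the time under the null.

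What is at stake is efficiency. This is a single-centre trial drawing on about 110 eligible-age births a year, so precision that can be had without recruiting more infants is worth having. The article names the primary test outright, so this is a stated choice and not a detail left to an analysis plan.

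**Working it through.** **Inputs.** From Sample size: mean 16.5 kPa, SD 4.7 kPa, normal shift 6 kPa, 20% effect, 80% power, two-sided 5%, 20% loss, 94 per arm. From Randomisation and allocation concealment: four strata, blocks of six. Assumed, because the article does not give it: R2, the share of outcome variance explained by the strata.

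**Step 1: reproduce 188.** The article does not give the effect in kPa. Taking 20% of the shift in excess of normal, 0.20 × (16.5 − 6) = 2.1 kPa:

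n per arm = 2 × [4.7 × (1.960 + 0.842) / 2.1]² = 78.6; 78.6 × 1.2 = 94.4, so 94 per arm and 188 in total.

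This matches. Taking 20% of the whole 16.5 kPa (3.3 kPa) gives 31.8 per arm, or 38.2 after × 1.2, which does not. The calculation uses the overall SD, so it is consistent with an unadjusted t test.

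**Step 2: precision with and without adjustment.** After 20% loss, 188 × 0.8 ≈ 150, or 75 per arm.

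- Unadjusted standard error: 4.7 × √(2/75) = 0.77 kPa. The 95% half-width is 1.52 kPa. Power ≈ Φ(2.1/0.7675 − 1.96) = Φ(0.776) = 78.1%.
- Adjusted residual SD: 4.7 × √(1 − R2), so the interval narrows by the factor √(1 − R2).

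| R2 (assumed) | Half-width, kPa | Power (normal approximation) |
|---|---|---|
| 0 | 1.52 | 78.1% |
| 0.05 | 1.48 | 80.2% |
| 0.10 | 1.44 | 82.2% |
| 0.20 | 1.36 | 86.4% |
| 0.30 | 1.27 | 90.5% |

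**Step 3: simulate the actual design.** Four strata, blocks of six, N = 188, 20% random loss, SD 4.7 kPa, 6,000 trials per scenario. The t test is compared with a linear model that includes the strata. Rejection rates are at a true difference of 0 (type I error) and 2.1 kPa (power).

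| R2 (assumed) | t test: type I error | t test: 95% CI coverage | Power, t test | Power, adjusted | Gain, points |
|---|---|---|---|---|---|
| 0 | 5.1% | 94.9% | 77.6% | 77.1% | −0.5 |
| 0.05 | 4.8% | 95.3% | 78.2% | 80.0% | 1.8 |
| 0.10 | 4.2% | 95.8% | 77.4% | 80.3% | 2.9 |
| 0.20 | 3.3% | 96.7% | 79.7% | 85.7% | 6.0 |
| 0.30 | 2.6% | 97.4% | 80.0% | 89.9% | 9.9 |

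The adjusted model holds about 5% type I error and 95% coverage throughout. Simulation error on each power figure is about √(0.8 × 0.2/6000) = 0.5 points, so the R2 = 0 row shows no real difference.

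**Step 4: express R2 as a gap between gestational bands.** With an assumed 40/60 split, R2 = 0.4 × 0.6 × gap² / 4.7² = 0.24 × gap² / 22.09. Gaps of 2, 3, 4 and 5 kPa correspond to R2 of 0.04, 0.10, 0.17 and 0.27. A separate simulation on this scale gave the following:

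| Gap, kPa | t test: type I error | Power, t test | Power, adjusted |
|---|---|---|---|
| 0 | 5.0% | 78% | 78% |
| 2 | 4.7% | 77% | 79% |
| 3 | 4.4% | 79% | 82% |
| 4 | 3.9% | 79% | 85% |
| 5 | 2.9% | 79% | 88% |

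The pattern is the same as in Step 3.

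**The case against.** The strongest reply is that the size rests on a figure that the article does not contain. A 4 or 5 kPa gap between bands is about twice the target effect of 2.1 kPa and 38% to 48% of the 10.5 kPa excess shift. At smaller gaps the gain is a point or two. The remark under Intervention concerns BPD risk in smaller infants. It says nothing about sex, and nothing about right shift among infants measured at 36 weeks. The SD of 4.7 kPa also comes from infants with moderate to severe BPD, not from all infants under 28 weeks. All of this stands, and it is why only the direction is firm, and only if the strata are prognostic.

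Three stronger readings may tempt a reader, and the article supports none of them.

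- *The t test interval is wrong.* It is unbiased and does not inflate type I error. At worst it is conservative, and a positive result would remain valid.
- *Ignoring the strata pushes power below the stated 80%.* The 78.1% at 75 per arm arises because 188 matches multiplying by 1.2 for attrition and not dividing by 0.8, which would give 99 per arm. That is a separate matter. The sample size assumes the overall SD and so matches the t test; what is forgone is power above that of the t test.
- *Every outcome should be adjusted.* For binary secondary outcomes, logistic regression changes the estimand to a conditional odds ratio and can be unstable for uncommon events at this size.

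**Conclusion.** The point holds as an efficiency matter. The design stratifies on two factors and the stated primary test discards them. If the factors predict right shift, which the article makes plausible for immaturity, the t test is conservative and its interval is wider than it needs to be.

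The gain from adjustment is nil at R2 = 0, about 1 to 3 power points at R2 of 0.04 to 0.10 (interval about 2% to 5% narrower), and about 6 to 10 points at R2 of 0.17 to 0.30 (about 9% to 16% narrower, from 1 − √(1 − R2)). These figures assume a 2.1 kPa difference, SD 4.7 kPa, about 75 measured infants per arm and loss unrelated to outcome. The value of R2 is unknown. The change is worth making because the factors are already recorded and little is lost if they prove uninformative. It is not a validity defect, and it does not call 188 into question.

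**What to change.** Before unblinding, replace the primary-analysis sentence under Statistical analysis with a linear model of right shift on treatment, sex and gestational age at birth, reporting the adjusted mean difference in kPa with its 95% confidence interval. Gestational age may enter as the randomisation band or as weeks at birth. The band mirrors the randomisation exactly; weeks assumes a linear relation. Choose one in advance. Keep the unadjusted t test as a supportive analysis.

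The cost is a sentence of text and one or two degrees of freedom out of about 150. Both variables are known at randomisation for every infant, the named statistical package fits the model, and the result is still a mean difference. Fixing the choice before unblinding keeps it from looking data-driven. Adjusted analysis of the binary secondary outcomes is optional and not part of this change.

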### Randomisation and allocation concealment

The infants will be stratified for randomisation according to the sex and gestational age at birth (23^0^ to 25^6^ and 26 to 27^6^ weeks). Infants will be randomised to treatments by the hospital pharmacist using a computer generated random table (REDCap) in blocks of six within the REDCap randomisation module [31]. The pharmacist will not have any clinical information regarding the recruited infant apart from stratification group and infant sex.

